**Methods:**

This mixed methods repeated measures pilot study will recruit 24 participants in 2 groups from 2 departments, the intensive care unit and the gastroenterology department. Participants from each group will take part in 3 unit-based Schwartz Rounds. Primary outcomes will include the study and intervention feasibility measures, while secondary outcomes will include scores on the Maslach Burnout Inventory–Human Services Survey, the Schwartz Centre Compassionate Care Scale, and the Culture of Care Barometer. Primary and secondary outcomes will be collected at baseline, after the Rounds, and 3-month follow-up. Two focus groups will be held approximately 2 months after completion of the Schwartz Rounds. Descriptive statistics, paired t tests, chi-square tests, and analysis of variance will be used to compare quantitative data across time points and groups. Qualitative data from focus groups and free-text survey questions will be analyzed using an inductive thematic analysis approach.

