### Participant Selection and Recruitment

As this is a pilot study of Schwartz Rounds in hospital settings, main eligibility criteria for participation in the study will include being employed at Mater Hospital and willingness to participate in all aspects of the study (focus group participation is not mandatory). Members of the research team and planning committee will be excluded from participation in the study to avoid any risk of bias. Participants will include both clinical staff (ie, nurses, doctors, allied health) and nonclinical staff (ie, administrative/managerial, catering and ward services, health security, pastoral care) employed at Mater Hospital.

Staff interested in participating in the Rounds will receive an email from the department head that will include the research flyer and the participant information and consent form, and they will be asked to return the signed consent form to the research team via email. Potential participants will be given the opportunity to receive further information and ask questions to the research team regarding the study over the phone or via email. Once consent forms have been received, participants will be sent a link to the online baseline survey to complete prior to commencement of Rounds. The surveys will be distributed by the study research assistant, via email, 1-2 weeks prior to each Round and returned by the day of the Round. Facilitators will meet with the panel members 2-3 weeks prior to each Round, for 1-2 hours, to discuss the topic and familiarize them with the Rounds processes.

During the study planning, the research team liaised with several Mater Hospital departments, and based on the staff interest and teams’ needs, selected 2 teams to participate, the intensive care unit (ICU) and the gastroenterology department. The study participants will therefore be recruited in 2 groups, the ICU group and the gastroenterology group, who will complete 3 unit-based Rounds each. The participants will complete a quantitative survey focusing on staff well-being, compassionate care, and organizational culture at baseline, after the Round, and 3 months’ follow-up. They will also complete a short postround feedback form after each Round that incorporates both Likert scale questions and an open-ended comment section. During consenting, participants will be invited to participate in a focus group session to provide detailed feedback on the Rounds. The flow of participants in the study is shown in Figure 1.

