Immediately after the completion of each Round, participants will be required to complete the Schwartz Centre Evaluation. After each Round, facilitators will complete a brief fidelity checklist and the research team will meet to discuss any immediate feedback. After the completion of 2 Rounds, an online survey link for the postrounds survey will be emailed to participants with a request to be completed within 1-2 weeks. Participants will be asked to complete surveys at baseline, after completing the Rounds, and at 3 months after the Rounds; attend at least two out of three Rounds; and provide immediate postround feedback. In addition, 3 participants per Round will be invited to participate as a panelist and share their stories and experiences in health care, making up the content of the Round.

To test the recruitment, delivery, and assessment procedures and inform any necessary adaptations prior to commencement of the study, the research team conducted an in-house pilot Round with the consultation liaison team. The 3 panelists, a psychologist, psychiatrist, and a psychiatric registrar, in discussion with the facilitators, agreed on the Round topic “When compassion is hard to find when caring for patients and their families.” The pilot Round was attended by 21 participants from a variety of nonclinical and clinical disciplines and their feedback on the Round as well as the study procedures was used to fine-tune the recruitment and data entry processes and incorporated in the study protocol. The participants’ feedback was overwhelmingly positive with 100% (21/21) of attendees reporting that the pilot Round gave them new insights into the perspectives and experiences of their co-workers, 86% (18/21) reporting new insights into the perspectives and experiences of their patients, 67% (14/21) reporting feeling better prepared to handle tough or sensitive situations, 76% (16/21) feeling less isolated in their work, and 95% (20/21) stating that they planned to attend future Rounds.

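### The post-Rounds survey is triggered after 2 Rounds of a 3-Round intervention, which contradicts the protocol's own definition of that time point

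*Protocol article*

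**What the plan says.** **Length of the intervention.** The abstract's Methods paragraph says "Participants from each group will take part in 3 unit-based Schwartz Rounds". Participant Selection and Recruitment describes the two groups as those "who will complete 3 unit-based Rounds each". Both give three Rounds.

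**Definition of the post time point.** The abstract says "Primary and secondary outcomes will be collected at baseline, after the Rounds, and 3-month follow-up". Schwartz Rounds Intervention and the Rounds Process asks participants to "complete surveys at baseline, after completing the Rounds, and at 3 months after the Rounds", and in the same sentence to "attend at least two out of three Rounds".

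**Operational trigger.** The sentence just before that one reads "After the completion of 2 Rounds, an online survey link for the postrounds survey will be emailed to participants", and it continues "with a request to be completed within 1-2 weeks". This is the only place where the article says when the link for the post survey is sent.

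**Other timing statements.** Participant Selection and Recruitment says that surveys are sent "1-2 weeks prior to each Round and returned by the day of the Round". Outcome Measures lists a pre-Round, a post-Round and a 3-month survey without saying which Round the middle one follows. The same section places the focus groups about two months after the third Round.

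**The concern.** The trigger sentence and the definition beside it cannot both hold for a three-Round intervention, and no section describes a survey after two Rounds as a deliberate interim measurement.

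The date matters because only three surveys are planned. The middle one is the sole immediate post-intervention reading of burnout, compassionate care and organizational culture. Data Management and Analysis relies on paired t tests, analysis of variance and post hoc comparisons of specific time points. If the middle survey falls before Round 3:

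- baseline to post measures part of the intervention;
- post to 3 months mixes any later change with the effect of a further Round;
- the start of the 3-month clock could be Round 2, Round 3 or the survey date.

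Study Design and Setting says that the pilot is meant to inform larger studies, so an ambiguous assessment schedule would be carried forward.

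**Working it through.** **1. The statements side by side**

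| Section | Statement | Round implied for the post survey |
|---|---|---|
| Abstract, Methods | three Rounds; outcomes after the Rounds | Round 3 |
| Participant Selection and Recruitment | three Rounds per group | Round 3, if post means after the intervention |
| Rounds Process, trigger sentence | link sent after 2 Rounds | Round 2 |
| Rounds Process, next sentence | survey after completing the Rounds | Round 3 |
| Outcome Measures | focus groups timed from the third Round | not a survey, but Round 3 is named as the end point |

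One sentence points to Round 2. The rest point to Round 3 or are silent.

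**2. Exposure at the survey under each reading of the trigger**

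The attendance rule (at least two of three) allows four patterns.

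| Rounds attended | If sent after the unit's Round 2: Rounds attended by then | If sent after the person's own second Round: sent after |
|---|---|---|
| 1, 2, 3 | 2 of 3 | Round 2 |
| 1, 2 | 2 of 3 | Round 2 |
| 1, 3 | 1 of 3 | Round 3 |
| 2, 3 | 1 of 3 | Round 3 |

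Under the first reading everyone has had at most 2/3 = 67% of the Rounds. Under the second, the calendar position of the time point depends on attendance, and anyone attending all three is still sent the survey before their last Round.

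Whether the 1-2 week window closes before Round 3 depends on spacing. The introduction describes Rounds in general as monthly. The article gives no spacing for this study, and the COVID-19 plan allows rescheduling. With monthly spacing (an assumption) the window closes first.

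**3. The plan's own figure**

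Sample Size and Statistical Power gives one group, m = 3 time points, f = 0.25, alpha 0.05, power 0.80, correlation 0.5 and N = 24. The usual within-subject formula is lambda = f² × N × m / (1 − rho), with df = m − 1 and (N − 1)(m − 1).

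- N = 24: lambda = 0.0625 × 24 × 3 / 0.5 = 9.0, df 2 and 46, power 0.74.
- N = 28 is the smallest N that reaches 0.80.

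So 24 does not reproduce from the stated inputs with three time points. (Four time points would give 24.) That is a separate matter and does not bear on the survey date. Below, 0.74 is the starting power.

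**4. Illustration of what an early survey could cost**

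Assumptions that are not in the article: the effect is fully present once the Rounds are complete and is maintained to 3 months (means 0, d, d in SD units), and two thirds of it is present after two of three Rounds.

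- Size of d: the SD of (0, 1, 1) is 0.4714, so d = 0.25 / 0.4714 = 0.53.
- Early survey: means 0, 2d/3, d = 0, 0.354, 0.530. Their SD gives f = 0.22.
- ANOVA at N = 24: lambda falls from 9.0 to 7.0, and power from 0.74 to 0.62.
- Baseline-to-post paired t test: with rho = 0.5 the SD of a difference is √(2 × (1 − 0.5)) = 1, so d_z = d. The noncentrality is 0.530 × √24 = 2.60 for the full effect (power 0.70) and 0.354 × √24 = 1.73 for two thirds of it (power 0.38).

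**The case against.** The strongest reply is that this is a slip in one sentence and not a chosen design. The abstract, the adjacent sentence and the focus-group timing all point to completion of three Rounds, and the number 2 may be loose shorthand for the attendance minimum. Figure 1, the participant flow, is not available here and may state the timing. This stands in part: the documents establish a contradiction, not that the measurement was in fact taken early. A correct figure would still leave the trigger sentence wrong, and the attendance reading produces the variable timing shown above.

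Four stronger inferences are tempting, and the documents do not support them.

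- **That the trial's main outcome is compromised.** These instruments are secondary. Feasibility is primary and rests on post-Round evaluations, focus groups, attendance and fidelity, none of which depends on this email.
- **That the analysis no longer estimates the effect of the intervention at all.** A survey 3 months after the Rounds follows the full intervention, so baseline versus 3 months remains interpretable (within the limits of an uncontrolled design), provided that the 3 months are not counted from Round 2.
- **That pre-Round distribution is a third, conflicting schedule for the post survey.** The sentence directly follows the one on the baseline survey and can be read as concerning only what is sent before a Round. It is unclear, but not a proven conflict.
- **That paired power falls from about 82% to 48%.** Those figures come from a difference of 0.612 SD, the end-to-end gap when f = 0.25 is spread over three equally spaced means. In time order that gap runs from baseline to 3 months. Baseline to post would be 0.306 SD, with power of about 0.30 at n = 24, so 82% is not a valid starting point for that comparison.

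**Conclusion.** The contradiction is real and rests on the text alone: three Rounds, a post survey defined as following them, and a trigger after two. Followed as written, the only immediate post-intervention measurement of the secondary outcomes is requested after at most two of three Rounds, the post-to-3-month comparison may include a further Round, and the 3-month anchor is undefined.

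The size of the effect on results cannot be derived from the documents. Under the stated assumptions (maintained effect, f = 0.25, correlation 0.5, two thirds of the effect present at the survey) the loss is about 0.12 in ANOVA power (0.74 − 0.62) and about 0.32 in paired baseline-to-post power (0.70 − 0.38). These are illustrations; the need to reconcile the text does not depend on them.

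**What to change.** - Send the post survey to all participants of a unit after that unit's third Round, whatever their attendance, and keep the 1-2 week return window.
- Count the 3-month survey from the same third-Round date.
- Make the abstract, Participant Selection and Recruitment, Rounds Process and Outcome Measures agree. State which surveys the pre-Round distribution sentence covers.

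Done prospectively, this costs a few sentences and one survey trigger date.

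It may be too late for that. The Results section reports recruitment complete in September 2021 and projects data collection to end by March 2022, before the article's publication in April 2022. If surveys have been sent, the remedy lies in reporting:

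- give the actual survey dates relative to each unit's Rounds, and the number of Rounds each person had attended before each survey;
- label any post survey completed before Round 3 as mid-intervention;
- use baseline versus 3 months as the comparison that follows the full intervention.

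This needs only the survey dates, the dates of each unit's Rounds and the attendance sheets that the study already plans to collect.

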### Data Management and Analysis

Qualitative and quantitative data will be collected by the research team through the self-report questionnaires, Rounds attendance sheets, postround feedback forms, and focus groups transcripts. Data will be deidentified and each participant will be given a number or pseudonym. All deidentified and identifiable data will be stored electronically on REDCap and Griffith University Research Space, where only the research team will have access to the data. All hard copy documents will be stored in a locked cabinet at Griffith University where only those that require direct access will be able to access it. Electronic information will be kept on encrypted devices. All data will be stored for 5 years and then destroyed in compliance with Griffith University and Mater Health policies. Upon study completion, deidentified data will be kept on the Griffith University repository after the final ethics report has been submitted.

Qualitative data from the open comment section of the standard postround evaluation form and focus groups transcripts will be thematically analyzed by 2 members of the research team [26]. Quantitative data will be analyzed using SPSS (IBM). Descriptive statistics, paired *t* tests, chi-square tests (or other suitable nonparametric tests), and analysis of variance will be used to compare survey data across time points and groups. Post hoc analyses will be conducted to compare differences between specific time points.

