### Outcome Measures

Participants will complete an online survey via REDCap at preround, postround, and 3-month follow-ups, which will collect demographic information and measures of staff well-being, compassionate care, and organizational factors. Demographic data will include age, sex, ethnicity, profession, length of time in profession, workload and typical roster, and length of employment at the Hospital.

Staff well-being will be measured using the Maslach Burnout Inventory–Human Services Survey (MBI-HHS) [27]. The MBI-HHS is a reliable and validated 22-item measure that measures burnout using 3 subscales: Emotional Exhaustion (α=.90), Depersonalization (α=.79), and Personal Accomplishment (α=.71), on a 7-point scale ranging from “never” to “everyday.” Compassionate care will be measured using the Schwartz Centre Compassionate Care Scale (SCCCS) – provider version [28,29]. The SCCCS consists of 12 items answered on a 10-point scale and has been shown to be reliable and valid for use with patients (α=.98) [29]. Organizational culture will be assessed using the Culture of Care Barometer – version 2 (CoCB-v2) [27]. The CoCB-v2 is a reliable and valid measure that consists of 30 items across 4 subscales: Organizational Values (α=.93), Team Support (α=.93), Relationships With Colleagues (α=.84), and Job Constraints (α=.70) [30,31].

In addition to these outcome measures, participants will be asked to complete the standard Schwartz Rounds Evaluation Survey at the end of each Round. This survey includes 10 questions answered with no, yes, or not sure; a question asking the participants to rate the Round overall as either poor, fair, neutral, good, or excellent; a free text question asking the participants to list 2 ways in which the Rounds will change how they related to or communicate with patients or colleagues; and an open comment section. Textbox 1 shows the Schwartz Rounds evaluation survey.

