### COVID-19 Risk Mitigation Plan

The impact of conducting Rounds in the context of COVID-19 challenges was discussed regularly during the study conception and planning. Research team considered the use of virtual Rounds in the planning stage but decided to proceed with the in-person Rounds, in view of the confidentiality and sensitivity and strong participants’ preference for in-person attendance that was indicated after the pilot Round.

Rounds planning included considerations of the reduced staff participation due to COVID-19–related quarantine, sick and family leave, low staffing levels on Hospital wards, and difficulties in accessing adequate room space to conduct the Rounds safely in accordance with COVID-19 social distancing requirements. The study COVID-19 risk mitigation plan specifies the personal safety and hygiene measures to be followed by the research team and participants, in compliance with Queensland Government and Mater Health COVID-19 guidelines. The measures include social distancing and may include mask wearing and rescheduling of the Rounds during acute lockdowns, in keeping with the government and organizational directives at the time the Rounds are scheduled.

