### Sample Size and Statistical Power

Participants will be recruited via a convenience sample. The required sample size was calculated using a power calculation for a repeated measures analysis of variance (one group measured across three time points) study using G*Power with effect size of 0.25 (*f*), α level of .05, power of 0.80, and correlation among repeated measures of 0.5. Therefore, it is calculated that a total sample size of 24 will be required for the study to be adequately powered to detect a significant difference (*P*<.05) between the time points. Approximately 10-15 participants will be selected from interested staff, to participate in 2 focus groups. This number of participants will ensure that 5-8 participants will take part in each focus group, in keeping with the recommended size for focus groups, and to ensure an even spread between professions, consistent with previous research recommendations [15,22].

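### The repeated measures ANOVA and paired t tests named for the survey scores use only complete sets of surveys; a mixed model in the same software would use every survey and lose less power

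*Protocol article*

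**What the plan says.** The Data Management and Analysis section says that SPSS will be used. It lists descriptive statistics and paired t tests, followed by "chi-square tests (or other suitable nonparametric tests), and analysis of variance will be used to compare survey data across time points and groups". It adds: "Post hoc analyses will be conducted to compare differences between specific time points".

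The section on the intervention and the Rounds process sets the waves: "Participants will be asked to complete surveys at baseline, after completing the Rounds, and at 3 months after the Rounds". The Sample Size and Statistical Power section identifies the ANOVA as repeated measures, with "one group measured across three time points", and arrives at 24 people. The abstract gives 24 as the number to be recruited, so there is no margin over the calculated number.

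The COVID-19 Risk Mitigation Plan says "Rounds planning included considerations of the reduced staff participation due to" quarantine, leave and low staffing. No figure for missing surveys appears anywhere in the article.

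**The concern.** A repeated measures ANOVA in SPSS works on one row per person and drops the row if any wave is missing. A paired t test drops a person only when one of its two surveys is missing. With three waves, the overall test and the three possible pairwise tests can therefore rest on up to four different sets of people, none using all the data collected.

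With 24 participants each dropped person matters. Two things are at stake. Power falls faster than the lost information requires. And the estimated change is biased if those who skip a follow-up differ in their earlier scores. One of the outcomes is burnout, so it is plausible that people with worse scores respond less.

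**Working it through.** **Inputs from the article.** N = 24, m = 3 time points, f = 0.25, alpha = 0.05, correlation rho = 0.5, target power 0.80 (Sample Size and Statistical Power).

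**Assumptions, because the article gives no figures.** Baseline is complete. A proportion q of participants misses each of the two follow-up surveys, independently, with q = 10%, 15% or 20%. Sphericity holds.

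**Step 1: the plan's own figure.** The within-subject formula has noncentrality lambda = N·m·f²/(1 − rho), with degrees of freedom m − 1 and (N − 1)(m − 1). For N = 24, lambda = 24 × 3 × 0.0625/0.5 = 9.0 on 2 and 46 degrees of freedom, and power is 0.74. Power of 0.80 needs N = 28 (lambda = 10.5, power 0.81). The stated 24 is therefore not reproduced by the stated inputs. That is a separate matter, but it means there is no slack even with full data.

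**Step 2: who is left.** The expected number of complete cases is 24(1 − q)². The two pairs that involve baseline keep 24(1 − q) people; the pair of the two follow-ups keeps 24(1 − q)².

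| q | All three surveys (ANOVA) | Baseline pairs (t test) | Post to 3 months (t test) |
|---|---|---|---|
| 10% | 24 × 0.81 = 19.4 | 21.6 | 19.4 |
| 15% | 24 × 0.7225 = 17.3 | 20.4 | 17.3 |
| 20% | 24 × 0.64 = 15.4 | 19.2 | 15.4 |

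**Step 3: power when loss is purely random.** The ANOVA figure is the step 1 formula averaged over the binomial number of complete cases. The comparison is a mixed model with one common within-person correlation, fitted to all available surveys. The true change is a step of 0.53 SD after baseline that is held at 3 months; this corresponds to f = 0.25, since 0.25/√(2/9) = 0.53.

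| q | Complete-case ANOVA | Mixed model | Difference |
|---|---|---|---|
| 0% | 0.74 | 0.74 | 0 |
| 10% | 0.63 | 0.71 | 0.08 |
| 15% | 0.58 | 0.70 | 0.12 |
| 20% | 0.52 | 0.68 | 0.16 |

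A simulation of 1,500 trials per setting gave 0.63 against 0.71 at 10%, and 0.53 against 0.68 at 20%.

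**Step 4: bias when loss depends on the baseline score.** Here the log-odds of missing a follow-up are assumed to rise by 1 per SD of baseline score. The true change from baseline to 3 months is −0.53 SD.

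| Setting | Mean complete cases | Complete-case change | Mixed-model change | Power, ANOVA | Power, mixed model |
|---|---|---|---|---|---|
| 10% | 18.3 | −0.43 SD | −0.53 SD | 0.43 | 0.71 |
| 20% | 14.5 | −0.35 SD | −0.54 SD | 0.26 | 0.68 |

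The complete-case estimate understates the change by 0.10 SD (0.10/0.53 = 19%) or 0.18 SD (0.18/0.53 = 34%).

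**The case against.** **Missing-data handling may be elsewhere.** An article commonly leaves it to the full protocol or analysis plan, and neither is shown. This stands: silence on missing data is no fault. The point rests only on the methods that the article does name.

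**The loss rates are assumed.** This also stands. A reader might infer that the COVID-19 section predicts missing surveys. It does not: it concerns attendance at in-person Rounds, while the surveys are emailed links. Hence the range rather than a single figure.

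**The named tests handle repeated data.** Correct. Both respect pairing, and a paired t test loses a person only from the affected pair. The weakness appears only when surveys are missing.

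**The mixed model is no cure-all.** Under purely random loss, complete cases are unbiased and only power is at stake. If people stop answering because of current burnout that was never recorded, the mixed model is biased too. It helps where loss depends on observed scores.

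**Chi-square.** A reader might infer that chi-square will be applied to the same people's answers over time as if they were independent. The text does not establish this. The sentence covers groups as well as time points, chi-square between units at one occasion is legitimate, and "or other suitable nonparametric tests" admits a paired test. The only repeated categorical outcome items described are the "10 questions answered with no, yes, or not sure" on the form completed after each Round, which has three options and no baseline.

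**Units.** A reader might also infer that comparing the two units contradicts a calculation made for one group. It does not: the power claim is only for differences between time points, and an unpowered exploratory comparison contradicts nothing.

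**Low stakes.** The scores are secondary outcomes of a feasibility pilot, and the Discussion concedes the small sample. This limits the weight of the point but is no reason to keep the less efficient method.

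**Conclusion.** The concern holds for the survey scores. The named ANOVA and paired t tests are valid for repeated data but make poor use of incomplete data, and their results can refer to different subsets of participants. At an assumed 10% to 20% loss per follow-up wave, complete-case ANOVA power is about 0.63 to 0.52, against about 0.71 to 0.68 for a mixed model and 0.74 with no loss. If loss follows the baseline score as assumed, the complete-case change is understated by roughly a fifth to a third, and the mixed model recovers it.

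These sizes depend on the assumed loss rates, a complete baseline, the plan's f and correlation, and a common correlation between waves. With no missing surveys the power difference disappears. The change is worth making, but no primary conclusion depends on it. The article reports that recruitment closed in September 2021, so the choice of analysis is the remaining way to limit the effect of missing surveys.

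**What to change.** In the Data Management and Analysis section, replace ANOVA and paired t tests for the survey scores with one linear mixed model per score:

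- SPSS MIXED, fitted by REML, with Satterthwaite or Kenward-Roger degrees of freedom.
- Fixed effects for time (three levels) and unit, with participant as the repeated subject and the covariance structure chosen beforehand.
- All available surveys included.
- Baseline-to-post and baseline-to-3-month changes reported with 95% confidence intervals, as the planned pairwise comparisons.

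State that the model assumes missingness depends only on observed data, and report the number of surveys at each wave.

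As a clarification only, say that chi-square or Fisher's exact tests serve comparisons between units at one occasion, and that any within-person categorical comparison uses a paired test.

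The cost is a change of wording and slightly more analysis work in the same software. No further data are needed.
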